## Abstract

**Background:**

Studies suggests a possible link between vaginal discharge and common mental distress, as well as highlight the implications of the subjective burden of disease and its link with mental health.

**Methods/Design:**

This is a community-based intervention trial that aims to evaluate the impact of a psycho-social intervention on medically unexplained vaginal discharge (MUVD) in a group of married, low-income Lebanese women, aged 18-49, and suffering from low to moderate levels of anxiety and/or depression. The intervention consisted of 12 sessions of structured social support, problem solving techniques, group discussions and trainer-supervised relaxation exercises (twice per week over six weeks). Women were recruited from Hey el Selloum, a southern disadvantaged suburb of Beirut, Lebanon, during an open recruitment campaign. The primary outcome was self-reported MUVD, upon ruling out reproductive tract infections (RTIs), through lab analysis. Anxiety and/or depression symptoms were the secondary outcomes for this trial. These were assessed using an Arabic validated version of the Hopkins Symptoms Checklist-25 (HSCL-25). Assessments were done at baseline and six months using face-to face interviews, pelvic examinations and laboratory tests. Women were randomized into either intervention or control group. Intent to treat analysis will be used.

**Discussion:**

The results will indicate whether the proposed psychosocial intervention was effective in reducing MUVD (possibly mediated by common mental distress).

**Trial Registration:**

The trial is registered at the Wellcome Trust Registry, ISRCTN assigned: ISRCTN: ISRCTN98441241

## Background

The Urban Health Study (UHS) undertaken in 2002-2003 provided the baseline survey data for the proposed intervention in Hey el Sellom. The UHS sample consisted of 3,100 households from three communities (Nabaa, Burj el Barajneh and Hay el Selloum) located in Beirut's poor and rapidly changing suburbs. All ever-married women (n = 1899) found in these selected households were subsequently interviewed to provide data on the social context of health, among which reproductive health.

The UHS findings indicated that abnormal vaginal discharge was a common complaint in Hey el Selloum. 38% of ever-married women aged 15-59 years in Hey el Sellom [1] complained of vaginal discharge, of whom 71% reported being 'bothered' by the complaint. Of those reporting vaginal discharge, 64% already consulted a health provider or planned to do so, of whom only a few actually reported having reproductive tract infections.

It has been estimated that more than half of the women in the Arab world suffer from symptoms associated with reproductive health problems; and the most commonly reported symptom is vaginal discharge [2-4]. Increasing evidence, on the other hand, indicates the poor association between reported symptoms of reproductive health problems and medically diagnosed diseases [5-9]. Vaginal discharge, being the most common reported gynaecological symptom of RTIs, has recently received more attention [1,5,10-12]. Patel V. *et al*., (2005), in a population-based survey conducted in Goa, India, showed the lack of association between complaints of vaginal discharge and the presence of medically diagnosed reproductive tract infections (RTIs). In another community-based study, conducted in three villages of Giza in Egypt, a similar finding was also observed. 77% of interviewed women in the study reported abnormal vaginal discharge, among whom 52% actually suffered from the presence of one or more RTIs [5]. In addition to the UHS, a study in Lebanon [6] conducted in Nebi Shite- Lebanese community, which shares similar socio-demographic characteristics to Hey el Sellom, showed similar observations. 24.5% of the women in the Nebi Shite survey reported vaginal discharge, while only 9.3% of these women actually suffered from RTIs.

From a woman's perspective, the subjective burden of self-perceived illness and abnormality can be as important as a result of disease due to a biomedical confirmed condition. For example, in Muslim communities, vaginal discharge is considered troublesome because it affects the woman's prayer requirements to be "clean" [7]. Self-perceived illness and abnormality also affect health-seeking behaviour, leading often to unnecessary spending on health care and ineffective management [8,9]. In fact, the syndromic management of vaginal discharge can lead to inappropriate treatment of a large proportion of women, as well as unnecessary spending on treatment of non-existing RTIs [8,13].

An alternative explanation to MUVD has been recently suggested. Several observational studies confirmed the contribution of anxiety and depression to medically unexplained gynaecological symptoms, such as pelvic pain and abnormal vaginal discharge [5,12,14-22]. Taking the already discussed UHS, the sub-sample analysis pertaining to Hey el Selloum sample, showed that a large proportion of women (42%) reported mental distress- as assessed by GHQ-12. Moreover, multivariate analysis showed that mental distress was significantly associated with reported abnormal vaginal discharge, after adjusting for relevant risk factors and reported RTIs [23]. Women considered stress to be a main cause of their discharge [24] and identified mental as well as psychological health as important elements contributing to their perception of good reproductive health [4]. The UHS also showed that both mental distress and reported gynaecological health problems were negatively associated with social support [25].

Along the same line, population-based studies from South Asia show significant associations between complaints of vaginal discharge and psychosocial stress, in addition to psychosomatic symptoms such as dizziness, backache, and weakness [12,14,26]. Qualitative studies in India indicated that women typically associate complaints of discharge with mental stress and related symptoms such as tiredness [12]. On the other hand, social support is consistently associated with common mental disorders (CMD) and physical conditions [27]. Improvements in social support were shown to lead to lower consultation rates [27,28] and reduced sickness absences [29].

These findings have important implications for alternative intervention strategies. Our proposed psychosocial intervention carried out in this trial (consisting of relaxing exercise and social support) aims to reduce MUVD as a result of reducing CMDs. There are only a few randomized controlled trials (RCTs) for the treatment of CMDs in the developing world [30-33]. Most of these studies have used traditional psychological models such as Cognitive Behavioural Therapy and/or Interpersonal Therapy to alleviate CMDs [34,35]. However, some studies in the West have shown the effectiveness of simpler alternative approaches such as problem solving [36,37] and group support strategies [30,38-43]. Similarly, different RCTs have demonstrated that progressive muscle relaxation and/or guided imagery can alleviate depressive symptoms by enhancing self efficacy and decreasing persistent unexplained physical symptoms [43-47].

We conducted a community-based randomized trial, comparing the experimental group (who were administered the psychosocial intervention) with the control group (who served as a treat later group). The research question is the following: **Does a community based psycho-social intervention **(combined structured social support groups and progressive relaxing exercises) alter **complaints from medically unexplained vaginal discharge **among low-income married women, aged 18-49 and residing in Hey el Sellom?

## Methods/Design

### Design

A community-based randomized trial was conducted to evaluate the impact of a psychosocial intervention on medically unexplained vaginal discharge (MUVD) in a group of married, low-income Lebanese women, aged 18-49, and suffering from low to moderate levels of common mental disorders (CMD) (anxiety and/or depression). The trial consisted of two arms: (a) Women in the experimental group who received psychosocial intervention, (b) women in the control group (treat later). The institutional review board of the American University of Beirut approved the study protocol.

### Setting & Study Population

The trial took place in Hey el Sellom, a neighbourhood located in the southern suburbs of Beirut, Lebanon. It is a large informal settlement of an estimated population of 150,000 (mainly Lebanese Shiites). The area suffers from official neglect and lacks basic health, education and physical infrastructure. Data from the UHS show that up to 60 per cent of inhabitants consider themselves 'poor'. Women have low education, with about 1 out of 4 women only reaching elementary school (1).

#### Study Inclusion Criteria

- Currently married women, 18-49 years of age

- Women who reported symptoms of vaginal discharge confirmed by medical exam to be MUVD

- Women who scored low to moderate levels of Common Mental Disorders (CMDs), based on the study screening tool for common mental disorders (Hopkins Checklist 25)

- Women who were willing to take part in the study by signing an informed consent after listening to our explanation of the study process

- Women who upon screening had none of the exclusion criteria listed below

#### Study Exclusion Criteria

- Pregnancy

- Menopause

- Less than 8 weeks postpartum

- Hysterectomy

- Women who score very low or severe levels of CMDs,

- Women who report having been treated for severe mental illness such as bipolar depression, schizophrenia and suicidal plans

### Sample Size

The sample size calculation was based on the primary outcome of reported MUVD at six months. Allowing for 10% attrition, a sample size of 80-102 in each group would provide 80-90% power to detect a difference of 20 percentage points (for example, 10% vs. 30%) in the proportion reporting MUVD at 6 months, using a 2-sided 5% significance level. There is no previous study that can directly inform the effect size likely for this outcome, but studies have found differences in recovery rates for CMD of up to 40% between usual care and active interventions for common mental disorders (4, 10, 11). We have opted for a 20 percentage point difference given these previous studies on CMD and our judgement that this is both a clinically significant and plausible difference in MUVD rates.

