### Intervention

The intervention package was given for six weeks. The package combined trainer-supervised relaxation exercises (twice per week for 30 minutes/session) and psycho-educational group discussions (twice per week for 75 minutes/session). The order of each session was determined by practical circumstances. The trainer-supervised relaxation exercises consisted of progressive muscle relaxation, guided imagery, stretching and breathing, and progressive resistance exercise. The psycho-educational sessions were divided into directed and semi-structured social support discussion sessions, incorporating problem solving skills building as well as venting. The relaxation exercises were given, over six weeks by trained physical fitness instructors, and the group discussions were given by clinical psychologists and assisted by co-moderates who were social workers. The fitness instructors were trained prior to the intervention by a specialist in muscle relaxation and guide imagery. Similarly, the clinical psychologists received two days of training from a senior clinical psychologist, and were provided with a manual that describes in detail each of the 12 sessions. To ensure coherence among group members, once a group was formed its members remained in the same group throughout the intervention period. The benefits to women enrolled in the trial included: the provision of free childcare during sessions, free pelvic exam, and free laboratory tests.

No major risks were anticipated for the participating women in this trial. There were potentially some discomforting issues, such as repeated pelvic exam and laboratory tests at baseline and at six months, an active commitment to attend sessions throughout the 6 weeks intervention periods, as well as answering some sensitive questions during the interview questionnaires. On the other hand, the control group were provided with a periodic mental health assessment during intervention delivery, free pelvic exam and laboratory tests at baseline and six months.

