### Analyses

The trial will be analyzed and reported in accordance with the CONSORT guidelines. An interim analysis was not planned for this trial. Descriptive statistics will be used to compare the two groups as randomized. The primary analysis will comprise the difference in the percentages of women with MUVD at 6 months between the groups as randomized (including the 95% confidence interval) and the number-needed-to-treat. Logistic regression analyses (for the primary and secondary outcomes) will be used to adjust for any baseline imbalances, and imputation methods will be used to replace missing outcome data. Clustering effects of the intervention groups will be accounted for using methods such as robust standard errors and mixed effects regression models. Potential mediators will be investigated by adding (separately) changes in HSCL-25 Anxiety and Depression sub-scales and the somatisation scale scores to the regression models with the primary outcome. Adherence to the intervention will be accounted for using instrumental variables regression models. Appropriate interaction terms will be added to the regression models for the primary and secondary outcomes to investigate differential effects of the intervention according to age and baseline HSCL-25 scores, all as continuous variables.

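### The sample size has no allowance for clustering although treatment is delivered in fixed groups, and the plan does not say that the cluster adjustment covers the primary difference and its interval

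*Protocol article*

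**What the plan says.** Three parts of the protocol article bear on this point.

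- **Sample Size.** "Allowing for 10% attrition, a sample size of 80-102 in each group would provide 80-90% power to detect a difference of 20 percentage points", with the illustration "for example, 10% vs. 30%) in the proportion reporting MUVD at 6 months", "using a 2-sided 5% significance level". The section mentions no group size, ICC or design effect.
- **Intervention.** Group discussions and supervised relaxation run twice a week for six weeks, and "once a group was formed its members remained in the same group throughout the intervention period". Under Randomization and Procedure, controls receive the intervention only after the six-month follow-up. No control woman is therefore in an intervention group before the primary endpoint.
- **Analyses.** The primary analysis is the difference between randomized groups in the percentage with medically unexplained vaginal discharge (MUVD) at six months, with a 95% confidence interval and the number needed to treat. Logistic regression for baseline imbalance and imputation come next, and then: "Clustering effects of the intervention groups will be accounted for using methods such as robust standard errors and mixed effects regression models".

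**The concern.** Women who share discussions, social support and the same leaders over 12 sessions may have correlated outcomes. The Analyses section accepts this; the power statement does not. If the correlation is positive, the intervention-arm percentage varies more than the sample size calculation assumes, and an analysis that allows for it has less power than the same calculation gives for independent women.

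The second issue is the reach of the clustering sentence. It follows the regression models and names methods by example, and nothing ties it to the primary difference in percentages. An analyst could report that difference with an ordinary two-sample interval and keep robust or mixed methods for the regressions. The headline interval would then be too narrow if outcomes are correlated within groups.

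**Working it through.** **Inputs from the Sample Size section.** Proportions 0.10 and 0.30, so difference d = 0.20 and mean 0.20; two-sided 5% (z = 1.960); power 80% or 90% (z = 0.842 or 1.282); equal arms; 10% attrition.

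**Step 1: reproduce the stated figures.** For independent women,

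n0 = [1.960·√(2·0.20·0.80) + z_power·√(0.10·0.90 + 0.30·0.70)]² / 0.20²

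This gives 61.6 (80%) and 82.0 (90%) per arm. The continuity correction, n = (n0/4)·[1 + √(1 + 4/(n0·d))]², gives 71.2 and 91.7. Dividing by 0.9 gives 79.2 and 101.9, which round up to the stated 80 and 102. Without the continuity correction, division by 0.9 gives 68.4 and 91.1, which does not match. The design effect in the published figures is therefore 1.

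**Step 2: allow for clustering in the intervention arm.** With m women per group, DE = 1 + (m − 1)·ICC multiplies the intervention-arm variance only:

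- SE under no difference = √[0.20·0.80·(DE + 1)/n]
- SE under the alternative = √[(0.10·0.90·DE + 0.30·0.70)/n]
- power = Φ[(0.20 − 1.960·SE under no difference) / SE under the alternative]

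Evaluable n is 80·0.9 = 72 and 102·0.9 = 91.8. For the continuity-corrected version, n is replaced by n − 2/d + 1/(n·d²), that is 62.3 and 82.1.

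The article states neither m nor ICC. With m = 10 **assumed**, power at 80/102 per arm is:

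| ICC | DE | Continuity-corrected | Uncorrected |
|---|---|---|---|
| 0 | 1.00 | 80% / 90% | 86% / 93% |
| 0.02 | 1.18 | 77% / 88% | 83% / 91% |
| 0.05 | 1.45 | 73% / 84% | 79% / 88% |
| 0.10 | 1.90 | 65% / 78% | 72% / 83% |

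Worked example at ICC 0.05, 80 per arm, corrected: the SEs are √(0.16·2.45/62.3) = 0.0793 and √[(0.09·1.45 + 0.21)/62.3] = 0.0739. Then (0.20 − 1.960·0.0793)/0.0739 = 0.60, and Φ(0.60) = 0.73.

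Over m = 8 to 15 and ICC 0.01 to 0.10, continuity-corrected power runs from 79% down to 58% at 80 per arm, and from 89% down to 71% at 102 per arm.

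**Step 3: the interval, if left unadjusted.** At 10% against 30%, the correct standard error of the difference exceeds the unadjusted one by √[(0.09·DE + 0.21)/0.30]. With m = 10 this factor is 1.03, 1.07 and 1.13 at ICC 0.02, 0.05 and 0.10. Over the wider range in step 2 it is 1.01 to 1.19.

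**The case against.** **The analysis already handles clustering.** This largely stands. The clustering sentence is not restricted to secondary models, and the article never says that the primary interval ignores clustering. A reader might infer that the primary interval is too narrow as planned. The text does not support that; it leaves the matter open, and the interval is too narrow only if the adjustment stops short of it.

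**There is no contradiction.** Sizing on independence and adjusting later is optimism about power rather than two incompatible statements. That is fair. What remains is a power figure that holds, by its own formula, only at an ICC of zero or below, in a plan that expects clustering.

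**The loss may be nil in practice.** This stands in part. If the final test has no continuity correction, the slack from that correction absorbs an ICC of 0.02 (83%/91%) and nearly absorbs 0.05 (79%/88%). At 0.10 the shortfall remains either way. The documents do not settle which row applies.

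**Other tempting extensions.** A reader might apply the design effect to both arms, which would overstate the loss because controls are not grouped before the endpoint. A reader might also cite the low power at 30% against 50%. Most of that comes from the different event rates: with no clustering at all, the continuity-corrected formula gives 63%/75% there. It is a separate matter.

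**Estimator choice belongs in the analysis plan.** Agreed. The precise variance estimator is detail that an article may leave out. Which result the adjustment covers is not, because it determines the primary interval.

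**Conclusion.** The power statement is wrong as written for the design described. The figures 80 and 102 contain no design effect, and by the formula that yields them any positive ICC puts power below 80% and 90% (apart from rounding slack of under one percentage point). That part rests on the article's own numbers.

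The size of the loss rests on assumptions. With groups of 10 it is about 2 to 3 percentage points at ICC 0.02, 6 to 8 at 0.05 and 12 to 15 at 0.10 by the continuity-corrected formula. The stated power is still met at ICC 0.02 if no continuity correction is used.

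On the primary interval the finding is conditional: the plan does not say that the cluster adjustment applies to the difference in percentages. If it does not, the interval is too narrow for any positive ICC, with a standard error understated by a factor of 1.03 to 1.13 in the cases above. If it does, only the wording needs attention.

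**What to change.** 1. **Restate power.** In Sample Size, apply 1 + (m − 1)·ICC to the intervention arm only, using the actual group size and a stated ICC range. Say whether the continuity correction is kept. Recruitment is described as done, so this restates what the trial can detect and asks for no extra women.
2. **Tie the adjustment to the primary result.** In Analyses, state that the primary risk difference and its 95% confidence interval are themselves adjusted for clustering in the intervention arm only, with each control woman treated as her own cluster. Because 80 to 102 women make up only a modest number of groups, name a small-sample correction, such as a bias-reduced (CR2) variance or Satterthwaite degrees of freedom. The exact choice can sit in the statistical analysis plan.

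**Cost.** A few sentences and a standard software option. The stated power will be slightly lower and the primary interval slightly wider.

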### Recruitment

Sample recruitment was facilitated by adopting a community-based participatory research approach. The recruitment of the women, the medical assessments, the data collection and the delivery of the intervention package was facilitated by our trial stakeholders: the Ministry of Social Affairs and Amel association. It was also facilitated by the assistance and support of the available schools, factories, gynaecological clinics, and satellite network providers found in the area. It was ensured that the different community counterparts were evenly distributed throughout the 11 different community neighbourhoods of Hey el Selloum. During recruitment, a baseline questionnaire was administered to determine whether or not the women initially met the trial's inclusion criteria. Women reporting vaginal discharge were referred to undertake a pelvic as well as laboratory check up- to rule out the presence of RTIs (following informed consent). Women who did not report any vaginal discharge were referred for a general physical exam, unless they insisted to undertake the pelvic and laboratory checkups.

### Randomization and Procedure

Randomization was performed using a computer-generated allocation schedule, produced by an individual not involved in the recruitment process. The original protocol was that the baseline measures and consent were planned to be obtained before allocation was determined remotely (by telephone) and then revealed to the woman. In the event, logistical constraints at the recruitment centres meant that remote allocation was not feasible and allocation was performed using the same computerized system as originally intended, but in the field rather than remotely. An unplanned consequence of this change in procedure was that the women were informed of their allocation before they gave written consent.

The women were informed of their allocation into either the intervention or the control arm (treat later and given the intervention after the 6 months follow up) when they returned to pick up their laboratory results. Women who did not obtain their results were contacted by telephone, up to a maximum of three times.

Blinding on the intervention status was not possible for both logistic and ethical reasons, especially as knowledge of involvement in the intervention was integral to its delivery.

